#### Control group

During the school year 2024/2025, users in the control group continued with access to their usual care, hence not gaining access to the intervention delivered through the IMPROVA platform. After the intervention period (school year 2024/2025), adolescents, families and, school staff in the control group will be able to access the IMPROVA platform during the school year 2025/2026 (wait-list control group).

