### IMPROVA platform

The IMPROVA platform incorporates two key components that constitute the primary modes of delivery for the IMPROVA intervention content:

Information platform: an open-access psychoeducational website, available in three tailored versions for adolescents, school staff, and parents. It serves as the central access point to the programme, providing general information, guidance on available resources, and access to the interactive modules on the intervention platform.Intervention platform: a password-protected eHealth platform (eSano), offering interactive training modules for adolescents and school staff.

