### IMPROVA information platform

The IMPROVA information platform (https://www.improva-info.eu/en/) complements the interactive training modules available on the intervention platform and serves as an openly accessible entry point to the IMPROVA programme. It requires no login and is designed to provide quick, easy-to-navigate psychoeducational tailored content for all stakeholder groups (adolescents, families, and school staff). Although less interactive than the modules in the intervention platform, the information platform was developed to be engaging and user-friendly. Features include info boxes, dropdown menus, images, and visual figures.

Each stakeholder-specific version also contains general information about the IMPROVA project, as well as topic-specific guidance, practical tips, and links to external resources. To support users in acute distress, a prominently placed emergency help button links to a dedicated help page listing country-specific support services, including hotlines, chats, and emergency contacts. Additional help resources are embedded into topic-specific pages (eg, support for individuals affected by (cyber) bullying). Finally, the information platform functions as a bridge to the intervention platform. A dedicated sub-page introduces the interactive modules, and topic-specific pages include links to corresponding modules for adolescents and school staff who wish to explore a topic further. Table 1 presents the contents presented to adolescents, school staff, and families in the information platform.

**Table 1 T1:** Contents of the IMPROVA information platform divided by target group

	Content for students	Content for school staff	Content for parents
1	Self-esteem	About IMPROVA	About IMPROVA
2	Strengths	Supporting students	Supporting my child
3	Emotions	Mental health (awareness)	Mental health (awareness)
4	Identity	Family-school collaborations	Family-school collaborations
5	Mental health	Tips for schools	Tips for families
6	Stress	Anti-bullying	Anti-bullying
7	Self-confidence	Child maltreatment	Child maltreatment
8	Mastering conflicts	Self-care for teachers	Self-care for parents
9	Heartache		
10	Relationships and sexuality		
11	Making friends		
12	Alcohol and drugs		
13	Sleep		
14	Physical activity		
15	Mind and body		
16	Social media		
17	Bullying		
18	School pressure and anxiety		

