#### Intervention group

Adolescents, families, and school staff in the intervention arm have access to the IMPROVA platform, which includes both the intervention and information platforms, once baseline assessments are completed. In each participating country, a designated support person was available to provide technical assistance to users throughout the trial via email.

None of the intervention components of the IMPROVA programme was mandatory or required to be completed. Therefore, all users were free to choose which parts of the intervention programme they wished to explore or engage with. This flexible approach was designed to respect the diverse needs and contexts of users, and to promote autonomy, allowing each participant—whether adolescent, family member, or school staff—to engage with the content most relevant and useful to their specific circumstances and interests.

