During the school year, the local research teams had close contact with a designated school representative, who acted as the main contact point with the project. In some schools, the contact occurred via WhatsApp, while other schools preferred emails or phone calls. These interactions served to organise the distribution of communication material with teachers, students, and families of the IMPROVA intervention programme. Diverse strategies were implemented to increase the visibility of the programme, such as posting information about the IMPROVA intervention on the school website, distributing flyers via the school channels to each stakeholder, or directly sending emails to participants. Once a month, a blog post about topics of interest to adolescents (eg, ‘procrastination’ and ‘FOMO—Why it’s okay to miss out’) was uploaded to the information platform, which also promoted usage of the intervention platform. Throughout the school year, schools also received posters to display on classroom notification boards. All these strategies aimed to raise attention to the intervention programme and the number of resources available for each user type. In summary, each user type received at least one communication material from IMPROVA every month, either directly via email or indirectly (eg, posting on the school webpage, posters), aiming to disseminate the project.

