### Technical data on intervention uptake (students and teachers)

Another outcome of the study is the uptake of the intervention. For the intervention platform, this includes basic usage data on how often and how participants have used the platform (eg, number of modules completed, which modules were completed). For the information website, this usage data comprises the number and sequence of user visits and the point of access (ie, the region). This information is essential to evaluate the interactions between usage and effectiveness and to assess the effectiveness of the various modules.

We also included a battery of assessments with parents, school staff, and at the school level that might provide meaningful information about the trial and could support the evaluation of the trial, such as potential mediators or moderators of effect.

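### The control arm is described as having no access to the platform-delivered intervention, but half of that platform was an open website, so the comparator is misdescribed and possible dilution is unmeasured

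*Protocol article*

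**What the plan says.** The *Control group* section states that during 2024/2025 "users in the control group continued with access to their usual care, hence not gaining access to the intervention delivered through the IMPROVA platform", with platform access to follow in 2025/2026.

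The *IMPROVA platform* section describes "two key components that constitute the primary modes of delivery for the IMPROVA intervention content". The first is public: "Information platform: an open-access psychoeducational website, available in three tailored versions for adolescents, school staff, and parents". The second is "a password-protected eHealth platform (eSano), offering interactive training modules for adolescents and school staff". The *IMPROVA information platform* section says of the first: "It requires no login and is designed to provide quick, easy-to-navigate psychoeducational tailored content for all stakeholder groups".

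The *Intervention group* section confirms that the platform's name covers both parts. Intervention users "have access to the IMPROVA platform, which includes both the intervention and information platforms, once baseline assessments are completed".

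On measurement, *Technical data on intervention uptake* says that for the information website "this usage data comprises the number and sequence of user visits and the point of access (ie, the region"). *Implementation evaluation* repeats this, treats usage data as needed to study how usage relates to effectiveness, and includes usage under adoption in Table 5.

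**The concern.** The comparator defines what the primary SDQ contrast estimates. As written, controls had none of the platform. By the article's own definitions, they were kept out of only one of its two parts. A reader of the trial result would take the contrast to be the full platform against nothing beyond usual care. The contrast that the design actually secured is narrower: eSano modules plus promotion of the programme, against usual care with the public website available.

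If some control pupils, parents or staff used the site, the intention-to-treat difference would normally shrink towards zero. A small or null result would then be hard to interpret, because the data described do not show how much control-arm use there was. For the same reason, website visits counted as uptake could mix intervention users, control users and the general public.

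**Working it through.** **Step 1. Who could reach what in 2024/2025, by the article's own definitions**

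| Component | Access | Students | School staff | Parents |
|---|---|---|---|---|
| Information website | open, no login | 18 topics | 8 topics | 8 topics |
| eSano modules | password | 22 modules | modules, with eight tutoring lesson plans | none |

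The counts come from Tables 1 to 3 and the staff-module section. The *Control group* statement can hold for the second row. It cannot hold for the first, which is nonetheless part of the platform. For parents the first row is the whole of the platform content. The condition in *Intervention group* that access begins after baseline cannot be enforced for the first row either.

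**Step 2. Can the described data show control-arm use?**

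- Website logs hold visits, sequence and region. No school, arm or participant identifier is described.
- *School recruitment and selection* names one recruitment region per country, and randomisation was within country, so both arms share each region. The article does not define the region recorded in the logs. If it is the recruitment region, it cannot separate the arms. If it is finer, no link to school or arm is stated.
- None of the adolescent or parent assessments listed asks about use of the site.
- *School-wide assessments* covers concurrent programmes, with the list still open. *Qualitative interviews* covers at least 10 to 15 volunteers per user type and country. Neither, as described, yields a control-arm exposure rate.

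**Step 3. What dilution would do (illustration only)**

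The plan's figures in *Sample size* are d=0.30, 80% power, α=0.05 (two-sided, from the analysis section) and N=6000. I could not reproduce 6000 from the stated inputs alone. The calculation gives 175 per arm, or 350 in total. The design effect is 1+(200−1)×0.20=40.8, so 350×40.8=14,280 analysed, and 14,280/0.5=28,560 enrolled. The within-person correlation for the two measurements is not given, so reproduction is undetermined. That question is separate. Here the stated 80% is taken as given.

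Let c be the share of the arm contrast lost. If a share p of controls use the site and it delivers a fraction f of the full effect, then c=p×f. With the standard error unchanged:

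- diluted effect = 0.30×(1−c)
- power = Φ((1.96+0.84)×(1−c)−1.96)
- N needed to restore 80% = 6000/(1−c)²

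| c | d | power | N to restore 80% |
|---|---|---|---|
| 0 | 0.30 | 80% | 6000 |
| 5% | 0.285 | 75.9% | 6649 |
| 10% | 0.27 | 71.3% | 7408 |
| 20% | 0.24 | 61.1% | 9375 |
| 30% | 0.21 | 50.0% | 12,245 |

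For example, p=10% gives c=10% only if the website delivers the full effect (f=1). With f=0.5 it gives c=5%. The documents give neither p nor f.

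**The case against.** A reader might infer that the planned contrast was not delivered. The documents do not support that. Open access makes exposure possible and does not show that it occurred. The interactive modules and the tutoring plans stayed behind a password. The article calls the website less interactive, and its student pages are short texts adapted from the modules. *Blinding, randomisation and allocation concealment* says that explanations were tailored to allocation, and *Intervention implementation strategies* says that resources were highlighted in intervention schools. Promotion such as "posting information about the IMPROVA intervention on the school website" could be seen by others, but the article does not show that it reached controls. A real contrast remained, of unknown size.

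A reader might also infer that contamination cannot be detected at all. That is supported only for the website logs as described. The school-level list was not final and interviews were planned, so some evidence of exposure could still emerge.

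Three further objections have force. The SDQ is adolescent self-report, so parents' reading of the site is an indirect route to the primary outcome. The larger losses of power require brief texts to carry much of a multi-level programme's effect. And mixed website traffic limits the interpretation of uptake rather than invalidating the implementation outcome, since module usage is described separately.

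None of this removes the conflict between the *Control group* section and the definition of the platform.

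**Conclusion.** The point holds as a misdescribed comparator with possible, unquantified dilution. The article attributes to the control arm a restriction that the design imposed on only one of two delivery modes. The other mode, including all platform content for parents, was open to both arms. The data described cannot assign website visits to an arm.

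The size is unknown. The power figures are conditional on an assumed loss of contrast and on the plan's own 80%. At a 10% loss, power would be about 71%. The direction, towards no effect, assumes that any use of the site by controls benefits them as it would intervention users.

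**What to change.** 1. Restate the comparator in *Control group* as usual care with no access to the password-protected eSano modules and with the public information website openly available. Reconcile *Intervention group* with this. Word the effectiveness conclusion to that contrast and name possible dilution as a limitation. Cost: wording, and a slightly less clean-sounding comparator.

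2. Report information-website visits separately, as public traffic not attributable to an arm. Do not count them as intervention-arm uptake or use them in analyses of effect by usage. Base attributable student and staff uptake on eSano usage. State that family uptake cannot be attributed from the logs, because eSano has no parent modules. Cost: a lower attributable uptake figure and no log-based figure for families.

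3. Optionally, if the January-February 2026 wave is still open, add one item in both arms asking separately about website use before and after summer 2025, and report it by arm as a rough estimate of contamination. Cost: one item, with recall error and some confusion with the access that controls are permitted in 2025/2026. If the wave has closed, the first two changes still apply.

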### Outcomes and assessments

Overall mental health is the primary effectiveness outcome of the IMPROVA intervention programme. Secondary outcomes include HRQoL, depression, anxiety, social isolation, and self-esteem.

The assessments administered in IMPROVA include scales in various domains and were conducted at baseline (between November 2024 and March 2025), mid-term (during the intervention, March–May 2025), postintervention (immediately after the intervention, May–August 2025; primary endpoint) and 6 months postintervention (January-February 2026, secondary endpoint). Schools dedicated a school class for baseline and postintervention assessments, so teachers and/or IMPROVA staff could support students during assessments.

A description of the assessments conducted in the IMPROVA project is provided in the following sections.

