### Effectiveness analysis

The effectiveness of the IMPROVA programme will be evaluated based on improvements in overall mental health. Specifically, the primary analysis of effectiveness will be reflected in a reduction in the total SDQ score. In addition, effectiveness will be assessed through improvements in the secondary outcomes, as specified in a preceding section.

A linear mixed-effects model will be used to assess the effectiveness of the intervention on continuous outcomes (SDQ total score) measured across three assessment points, and generalised estimating equations will be used for categorical outcomes. Adolescents will be nested within schools, and schools will be nested within the four countries. A complementary analysis will include all four time points to evaluate the potential intervention effects at follow-up.

The model will include fixed effects for time, group (intervention vs control), and their interaction (group×time), which captures the differential change over time attributable to the intervention. The interaction term will be the main parameter of interest for assessing intervention effectiveness. To account for the multilevel design, the model will include a random intercept for each participant to account for repeated measures, a random intercept for each school to adjust for within-school clustering, and a fixed effect for country to control for systematic differences across national contexts. Other covariates associated with the outcome may be included in the model as fixed effects, depending on the objective. All models will be adjusted for the sex and age of the student.

The effectiveness analyses will be carried out following the intention-to-treat principle. In addition, a complete case analysis will be conducted as a sensitivity analysis to assess the robustness of the findings. Differences between included and excluded participants will be examined to explore potential bias due to missing data.

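### The 6-month follow-up falls inside the school year in which wait-list controls get the platform; if access opens first, the follow-up contrast is early versus delayed access, not intervention versus control

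*Protocol article*

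**What the plan says.** Three sections of the protocol article bear on this point.

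- **Control group.** The unexposed period is tied to one school year: "During the school year 2024/2025, users in the control group continued with access to their usual care, hence not gaining access to the intervention". Adolescents, families and school staff "in the control group will be able to access the IMPROVA platform during the school year 2025/2026 (wait-list control group". No opening month is given, and access is not made conditional on completing the follow-up assessment.
- **Outcomes and assessments.** The two endpoints are timed as "postintervention (immediately after the intervention, May–August 2025; primary endpoint) and 6 months postintervention (January-February 2026, secondary endpoint". Table 4 schedules the SDQ and every secondary scale at follow-up.
- **Effectiveness analysis.** The main model covers "continuous outcomes (SDQ total score) measured across three assessment points". It takes as its parameter of interest the fixed effects' "their interaction (group×time), which captures the differential change over time attributable to the intervention". Then: "A complementary analysis will include all four time points to evaluate the potential intervention effects at follow-up". The section gives no different reading of the group×time term at follow-up.

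**The concern.** The last assessment wave lies within the only period in which the document places control access. Taken as written, the plan allows control schools to use the programme for some time before the wave that is meant to measure its longer-term effect. The analysis would still label the arm difference there as attributable to the intervention.

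What is at stake is the meaning of a named secondary endpoint. If the programme works and controls begin to use it, the arms converge because the controls improve. A reader of the four-time-point analysis would see a smaller contrast at follow-up than at postintervention and could conclude that the effect had faded in the intervention arm. The arm contrast alone cannot separate the two explanations.

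**Working it through.** The plan gives no figure to reproduce. The check is one of dates, followed by an illustration of size.

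**1. Order of events**

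| Event | Stated timing | Section |
|---|---|---|
| Controls without access | School year 2024/2025 | Control group |
| Postintervention (primary endpoint) | May–August 2025 | Outcomes and assessments |
| Control access | At some point in school year 2025/2026 | Control group |
| Follow-up (secondary endpoint) | January–February 2026 | Outcomes and assessments |

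The primary endpoint and the three-point model come before wait-list access. The follow-up wave lies inside the access year. Whether access precedes the wave depends on a month that the article does not state.

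**2. Possible length of prior control access**

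Assume, for the early extreme, that access opened on 1 September 2025. From then to 1 January 2026 is 122 days, and to 28 February 2026 it is 180 days, so about 4 to 6 months. At the late extreme, access opens after February 2026 and prior exposure is zero.

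For scale, the Intervention group section gives intervention schools access once baseline is complete. Baseline ran until 16 March 2025 (Participants section), and postintervention began in May 2025. From 16 March to 1 May is 46 days, the shortest exposure that the stated windows allow. Control exposure of several months would therefore not be trivial by comparison.

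**3. Effect on the contrast**

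Let d be the effect of the programme and c the share of it that controls have gained by follow-up, with the intervention arm keeping its full effect. The expected contrast is (1 − c) × d. Take d = 0.30, 80% power and α = 0.05 from the Sample size section, with two-sided tests as the article states. Treat the planned power as given, without re-checking the sample size. Then:

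power = Φ[(1.960 + 0.842)(1 − c) − 1.960]

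| c (assumed) | Expected contrast | Power |
|---|---|---|
| 0 | 0.30 | 80% |
| 0.25 | 0.225 | 56% |
| 0.50 | 0.15 | 29% |
| 0.75 | 0.075 | 10% |
| 1 | 0 | 2.5% (one-tail error rate only) |

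The document gives no control uptake, so no row can be singled out as likely.

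**4. The interval label**

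- Shortest: 31 August 2025 to 1 January 2026 = 123 days; 123 / 30.44 = 4.0 months.
- Longest: 1 May 2025 to 28 February 2026 = 303 days; 303 / 30.44 = 10.0 months.

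These pair the extreme ends of windows that cover all four countries. They bound the interval and do not describe its spread.

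**The case against.** The strongest reply is that nothing here is shown to go wrong. The Control group section names a school year, not a month. Opening the platform in March 2026 would satisfy every sentence in the article and leave the follow-up contrast clean. An opening date is also an operational detail that an article may leave to the full protocol. The primary endpoint is safe, the follow-up analysis is called complementary, and the comparison stays randomised in any case.

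Much of this stands, and it limits the point. A reader might infer any of the following, and the document does not support them:

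- **That the follow-up contrast is already invalid.** This would need access before the wave, which is not stated.
- **That catch-up would be large or complete.** No component is mandatory (Intervention group section), and no control uptake is reported. The values of c above are assumptions.
- **That harm would go unseen.** Harm arising during the intervention year would still show at the postintervention primary endpoint. Only later or persisting harm could be obscured at follow-up.
- **That intervals really range from 4 to 10 months.** No school is said to have either extreme pairing. Both arms share the windows and randomisation was blocked within country, so no arm bias follows from the interval.
- **That the primary comparison is contaminated too, because the information site is public** ("It requires no login and is designed to provide quick, easy-to-navigate psychoeducational tailored content for all stakeholder groups"). That is a separate matter: it does not arise from wait-list access, and no figure for use by control schools is given.

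What the reply does not remove is that the article does more than omit a date. It commits to an access window that contains its own secondary endpoint, and it commits to reading the arm difference at that endpoint as the intervention effect. Following both statements can put a wrong causal label on the result.

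**Conclusion.** The concern holds in conditional form. If control access opens before the January–February 2026 wave, the follow-up contrast is a randomised comparison of early with delayed access. Bias relative to intervention versus no intervention would usually be towards no difference. Its size is (1 − c) × d for an unknown c: at d = 0.30 it could run from no dilution (c = 0) to no remaining contrast (c = 1), with 0.15 at an assumed c of 0.5.

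This should be fixed, but it does not threaten the trial's main result. Only the secondary endpoint and the four-time-point analysis are touched, since the postintervention analysis precedes wait-list access. The conclusion rests on the stated dates and on the absence of any stated hold-back. It would fall away if access was in fact opened only after follow-up was complete.

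**What to change.** 1. Reconcile the Control group, Outcomes and assessments, and Effectiveness analysis sections, so that the order of control access and the follow-up wave is explicit.
2. Record for each control school the date access opened and the date of its follow-up assessment. Use the intervention-platform usage logs, already planned under technical data on intervention uptake, for control users as well. The article does not say whether they cover controls once access opens.
3. Where access came first, define the follow-up contrast before analysis as early versus delayed access, and keep the intervention-versus-control claim at postintervention. If opening dates differ between control schools, the contrast should still include all schools as randomised, because the order of opening was not itself randomised.
4. Report the actual time from postintervention to follow-up in place of a uniform 6-month label.

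The cost is one date field per control school, an extract from existing logs and a redefined secondary contrast. No new participants are needed and the primary analysis does not change. The real loss is that the plan gives up an intervention-versus-no-intervention claim at follow-up for schools with prior access.
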